# Efficacy of metformin and fermentable fiber combination therapy in adolescents with severe obesity and insulin resistance: study protocol for a double-blind randomized controlled trial

**DOI:** 10.1186/s13063-021-05060-8

**Published:** 2021-02-17

**Keywords:** Adolescents, Insulin resistance, Diabetes, Obesity, Metformin, Dietary fiber, Gut microbiome

## Abstract

**Background:**

Accumulating evidence suggests that the metabolic effects of metformin and fermentable fibers are mediated, in part, through diverging or overlapping effects on the composition and metabolic functions of the gut microbiome. Pre-clinical animal models have established that the addition of fiber to metformin monotherapy improves glucose tolerance. However, possible synergistic effects of combination therapy (metformin plus fiber) have not been investigated in humans. Moreover, the underlying mechanisms of synergy have yet to be elucidated. The aim of this study is to compare in adolescents with obesity the metabolic effects of metformin and fermentable fibers in combination with those of metformin or fiber alone. We will also determine if therapeutic responses correlate with compositional and functional features of the gut microbiome.

**Methods:**

This is a parallel three-armed, double-blinded, randomized controlled trial. Adolescents (aged 12–18 years) with obesity, insulin resistance (IR), and a family history of type 2 diabetes mellitus (T2DM) will receive either metformin (850 mg p.o. twice/day), fermentable fibers (35 g/day), or a combination of metformin plus fiber for 12 months. Participants will be seen at baseline, 3, 6, and 12 months, with a phone follow-up at 1 and 9 months. Primary and secondary outcomes will be assessed at baseline, 6, and 12 months. The primary outcome is change in IR estimated by homeostatic model assessment of IR; key secondary outcomes include changes in the Matsuda index, oral disposition index, body mass index *z*-score, and fat mass to fat-free mass ratio. To gain mechanistic insight, endpoints that reflect host-microbiota interactions will also be assessed: obesity-related immune, metabolic, and satiety markers; humoral metabolites; and fecal microbiota composition, short-chain fatty acids, and bile acids.

**Discussion:**

This study will compare the potential metabolic benefits of fiber with those of metformin in adolescents with obesity, determine if metformin and fiber act synergistically to improve IR, and elucidate whether the metabolic benefits of metformin and fiber associate with changes in fecal microbiota composition and the output of health-related metabolites. This study will provide insight into the potential role of the gut microbiome as a target for enhancing the therapeutic efficacy of emerging treatments for T2DM prevention.

**Trial registration:**

ClinicalTrials.gov NCT04578652. Registered on 8 October 2020.

**Supplementary Information:**

The online version contains supplementary material available at 10.1186/s13063-021-05060-8.

## Administrative information

The order of the items has been modified to group similar items (see http://www.equator-network.org/reporting-guidelines/spirit-2013-statement-defining-standard-protocol-items-for-clinical-trials/).

## Introduction

### Background and rationale {6a}

Childhood obesity is a major risk factor for the development of insulin resistance (IR) and type 2 diabetes mellitus (T2DM) in youth. Importantly, youth-onset T2DM has been delineated as a more aggressive disorder, characterized by severe IR, insulin hypersecretion, rapid β-cell deterioration, and poor response to standard therapies [1–4]. Although limited or modest success has been reported for lifestyle interventions with behavioral modifications, such as diet and physical activity, they remain the most commonly applied therapies for IR and the underlying obesity in both adults and adolescents [1]. Pharmacotherapy with metformin (MET) has shown to induce modest reductions in body mass index (BMI) and reverse glucose intolerance in adult-onset T2DM [5]. However, for youth-onset T2DM, MET monotherapy has shown a 52% failure rate, while MET plus intensive lifestyle therapy also has shown a failure rate of 47%, as estimated by an uncontrolled intervention trial [1, 4]. Therefore, a clear need exists for the identification of efficacious therapies in adolescents which could be added to lifestyle modifications.

Adolescents with obesity typically present with systemic low-grade inflammation that has been implicated in the development of IR and cardiovascular dysfunction [6]. Obesity has also been associated with an imbalance in the composition and functionality of the gut microbiota [7–9]. However, it is unclear if changes in the gut microbial community contribute to the pathophysiology of adolescent obesity and associated comorbidities [10–12]. Gut microbiota might influence obesity and its dysregulated immunometabolism by facilitating caloric recovery [13], altering intestinal barrier and immune homeostasis [14], promoting the release of incretins and satiety hormones such as glucagon-like peptide 1 (GLP-1) [15], and regulating intestinal and hepatic gluconeogenesis [16]. Research further suggests that the composition of the gut microbiota can alter the risk of developing IR. For instance, the abundance of *Akkermansia muciniphila* has been inversely associated with obesity and IR [17–19]. On the other hand, *Prevotella copri* and *Bacteroides vulgatus* have been positively associated with the biosynthesis of branched chain amino acids (BCAAs), which are linked to the development of IR [20, 21]. Finally, the translocation of microbially derived lipopolysaccharides, termed endotoxemia, has been observed in patients with metabolic syndrome and T2DM [17, 22]. Despite the relationship described before, causal links between IR and the human gut microbiota remain to be established.

Effects of MET on glucose homeostasis are mediated through increases in hepatic insulin sensitivity, intestinal glucose utilization, anorexigenic GLP-1 levels, and reductions in hepatic glucose production [23]. At least some of the effects of MET are thought to be mediated by the gut microbiota. Recently, Wu and colleagues investigated the effect of MET on the composition and metabolic functions of the gut microbiota using a parallel-armed, randomized, placebo-controlled study in adults with newly diagnosed T2DM [24]. On an energy restricted diet, both groups reduced BMI significantly; however, only the MET group demonstrated reductions in fasting blood glucose and hemoglobin A1c (HbA_1c_) after 4 months. MET was found to increase the fecal abundances of *Bifidobacterium adolescentis* and *A. muciniphila*, with both species further shown to utilize MET for growth in vitro. However, HbA_1c_ reductions were only associated with changes in *B. adolescentis*, suggesting a positive link between MET-improved glycemic control and the abundance of *B. adolescentis* [24]. More recently, administration of *A. muciniphila* has been shown to improve insulin sensitivity in adults with obesity and IR [25].

Dietary fibers have been long implicated in the protection from obesity and related comorbidities [26, 27]. As dietary fibers are not digested in the small intestine, they serve as growth substrates for the gut microbiota, producing putatively beneficial metabolites such as short-chain fatty acids (SCFAs) upon degradation [28, 29]. Microbially derived SCFAs have been proposed to enhance intestinal barrier function, downregulate pro-inflammatory immune responses, alter gastrointestinal transit time, reduce hepatic-associated gluconeogenesis, improve insulin sensitivity, and promote satiety independent of GLP-1 [29–31]. Administration of SCFAs in humans has also been shown to improve glucose metabolism, systemic inflammation, and energy homeostasis [30]. In addition, consumption of diets rich in dietary fiber can limit microbial fermentation of proteins and production of potentially detrimental metabolites, such as *p*-cresol, amines, and branched chain fatty acids [29, 32, 33]. Since MET and fermentable fibers have been shown to reduce weight and increase insulin sensitivity through divergent mechanisms of action, we postulate that combination therapy with MET plus fiber will act in concert to increase insulin sensitivity in adolescents with obesity through synergistic effects on the gut microbiome.

Pre-clinical studies in animal models of diabetes confirm that the addition of fermentable fibers, such as type-III resistant starch [34], PolyGlycopleX® (PGX) [35], and konjac mannan oligosaccharides [36], to MET monotherapy enhances glycemic control and delays T2DM progression. While evidence in humans remains limited, a short-term, uncontrolled study in adolescents showed that MET plus fiber (Policaptil Gel Retard®) promoted greater weight loss than MET alone; however, links to the gut microbiome were not elucidated [37]. In adults, the addition of inulin, oat β-glucan, and blueberry-derived polyphenolics to MET monotherapy has been shown to improve both glycemia and the gastrointestinal tolerance of MET after 2 weeks [38]. Furthermore, consumption of either supplemental fiber or a high-fiber diet promoted weight loss and improved HbA_1c_ in adults with T2DM on MET monotherapy [39]. Overall, these findings suggest that separate pathways underlie the effects of MET and fermentable fibers, as fermentable fibers enhanced responses to MET. Thus, gut microbiome-targeted MET plus fiber combination therapies may have potential for enhanced reduction of IR in adolescents with obesity. The aim of this study protocol is to compare the effects of MET and fiber alone and in combination over 12 months on measures of insulin sensitivity and resistance in adolescents at high risk of T2DM.

### Objectives {7}

The primary objective is to compare the efficacy of MET (850 mg p.o. twice/day) versus FIBER (35 g/day supplemental fiber) alone versus combined MET plus FIBER on IR (as estimated by homeostatic model assessment of insulin resistance [HOMA-IR]) in adolescents with obesity, IR, and family history of T2DM.

The secondary objective is to compare the effects of the study therapies alone or in combination on:
Changes in the Matsuda, insulinogenic, and oral disposition indices as determined by OGTTChanges in body weight, BMI percentile and *z*-score, and body composition (fat mass, fat-free mass, and fat mass to fat-free mass ratio)Changes in quality of life (QoL) and perceived hunger and satietyChanges in fasting metabolic (glucose, adiponectin, and lipids) and satiety markers (acylated ghrelin, peptide tyrosine tyrosine [PYY], GLP-1, and leptin)Changes is measures of systemic inflammation (C-reactive protein, interleukin 6, and tumor necrosis factor-α [TNF-α]) and intestinal barrier function (lipopolysaccharide-binding protein (LPB) and fecal calprotectin)Changes in gut microbiome composition and functions (fecal microbiota composition, fecal SCFAs and bile acids, and targeted plasma metabolomics [amino acids, branched chain ketoacids, acylcarnitines, ceramides, trimethylamine *N*-oxide, choline, and betaine])

### Trial design {8}

A single-center, parallel three-armed, double-blinded, 12-month randomized controlled trial with a 1:1:1 allocation ratio. Ninety adolescents (*n* = 30 per arm) with obesity, IR, and family history of T2DM will be enrolled in the trial matched for sex and age (Figs. 1 and 2).

**Fig. 1 Fig1:**
[figure not shown]
Study design. Participants meeting the eligibility criteria will be randomly allocated to one of three study groups: (1) metformin (850 mg bid), (2) fiber (supplemental fiber 35 g/day) or metformin plus fiber. Participants will be followed up for 12 months with clinical visits every 3 months. Abbreviations: ADP, air displacement plethysmography; BMI, body mass index; HOMA-IR, homeostatic model assessment of insulin resistance; T2DM, type 2 diabetes mellitus

**Fig. 2 Fig2:**
[figure not shown]
Conceptual design. Changes expected in primary and secondary outcomes in the combination therapy compared to each monotherapy. Symbols: ↑ increase or improvement; ↓ decrease

## Methods: participants, interventions and outcomes

### Study setting {9}

Participants will be recruited from both the Pediatric Endocrinology and General Pediatric Clinic at the Stollery Children’s Hospital at the University of Alberta (UofA), and the community based Pediatric Centre for Weight and Health in Edmonton, Canada.

### Eligibility criteria {10}

Inclusion criteria:
Age 12–18 years oldBMI ≥ 95th percentile for age/sexTotal weight fluctuation over past 6 months < 10%HOMA-IR > 3.16Family history of T2DM (first- or second-degree relative)

Exclusion criteria:
Current use of insulin or diagnosis of T2DMSystolic or diastolic blood pressure > 99th percentile for age and sexAcute infectious or inflammatory condition over the preceding 1 month; hospitalization > 48 hHistory of chronic diseases, such as liver, kidney, or inflammatory bowel disease, or neurologic disordersActive malignancyConcomitant use of medication/investigational drug known to affect body weight in the past yearAntibiotic use in past 60 days; probiotic and/or prebiotic supplement use in the past 30 days; use of lipid-lowering and anti-inflammatory medication

### Who will take informed consent? {26a}

Written informed consent (from parents/caregivers and participants aged 18 years) and assent (from participants aged 12–17 years) will be obtained from all participants before inclusion by the principal investigator or trained research staff.

### Additional consent provisions for collection and use of participant data and biological specimens {26b}

Participants will be asked to provide Optional Specimen Consent to biobank blood and stool samples for future studies yet to be determined. Participants who do not consent for biobanking can still take part in the rest of the study.

## Interventions

### Explanation for the choice of comparators {6b}

We postulate that the therapeutic effects of both MET and fermentable fibers are mediated, in part, through diverging effects on the gut microbiome, and that MET plus fiber combination therapy will act synergistically to improve glucose tolerance in adolescents with obesity and IR. By combining MET with fiber, we anticipate that the improvement in IR and BMI will be significantly higher when compared to each monotherapy. A control group without treatment is not included, since a no treatment arm would be unethical for adolescents with obesity and IR.

### Intervention description {11a}

Participants will be randomly assigned to one of three study arms:
MET arm: MET (850 mg p.o. twice/day—standard of care) plus fiber placebo dailyFIBER arm: fiber supplementation (35 g/day fiber) plus MET placebo twice/dayMET + FIBER arm: MET (850 mg p.o. twice/day) plus fiber supplementation (35 g/day fiber)

### Metformin administration and rationale

Participants in the MET group will initially receive 500 mg daily, increasing to 500 mg twice/day if tolerated after 2 weeks (those who do not tolerate will be withdrawn from the study), and then increasing after an additional 2 weeks to 850 mg twice/day (1700 mg daily). The MET or placebo (microcrystalline cellulose [MCC] powder) capsules will be taken with meals along with a multivitamin containing B12, in order to prevent a potential MET-associated vitamin B12 deficiency [40]. A dose of 850 mg twice/day was chosen based on studies demonstrating decreases in BMI and IR at these doses [41, 42]. Although side-effects of MET are generally minor, the dosage will be titrated to avoid mild, self-limited side-effects (i.e., abdominal pain, flatulence, bloating, nausea, and diarrhea). Although lactic acidosis, hypoglycemia, and other serious side-effects are rare, side-effects will be routinely monitored throughout the trial by the principal investigator or a research coordinator.

### Fiber administration and rationale

Our supplemental fiber mixture (35 g/day of total fiber) will be composed of fermentable non-viscous (6 g oligofructose + 12 g resistant maltodextrin + 12 g acacia gum) and viscous (5 g PGX) fibers. Dosages of individual fibers were determined based on clinical evidence for effective dose and known tolerability data (Additional file 1). In addition, we and others suggest that ~ 50 g/day of fiber (35 g/day supplemental + ~ 15 g/day from diet) may be required for attaining reliable physiological benefits linked to fiber [29, 43]. This conclusion is supported by recent findings that 35 g/day of fermentable fiber maximized the health-relevant shifts in both bacterial taxa and fecal SCFAs [33]. Previous pediatric dietary fiber interventions of similar dosage report no tolerance concerns [44, 45]. For instance, Zhang et al. provided children with obesity around 50 g/day of fiber without any concerns of tolerance [45]. While it is expected that 35 g/day of fermentable fiber will be tolerated, gastrointestinal symptoms will be monitored throughout the trial.

To allow time for gastrointestinal adaptation, participants will be instructed to use ^1^/_3_ of the total daily fiber dose (or placebo) during the first week of treatment; then ^2^_/3_ of the dose for the second and third weeks; and then the full dose thereafter. This dose escalation is suggested to improve tolerance as adaption over time has been previously described for such fiber supplements [46, 47]. The fiber treatment (or placebo) will be provided as a powder to be added by the participant to water or sugar-free beverages and consumed prior to meals. This method of consumption is easy to incorporate and ensures enough water intake is spread throughout the day to improve gastrointestinal tolerance. Alternatively, participants will be allowed to mix the fiber, or placebo, with foods (e.g., added to cereals, soups, and yogurt), if preferred, to allow flexibility and maximize compliance, which is important due to the duration of the intervention. The fiber placebo will consist of MCC, a non-fermentable fiber with no effect on the gut microbiota [48].

### Criteria for discontinuing or modifying allocated interventions {11b}

Participants will be withdrawn from the study if the participant (1) withdraws consent, (2) becomes pregnant, (3) does not tolerate either MET or dietary fiber interventions, (4) requires antibiotic therapy within the first 6 months of the trial, (5) has an HbA1c > 8%, or (6) the participant, in the opinion of the investigator, is not clinically able to continue to follow the investigative intervention (e.g., need of initiating another specific medical intervention such as insulin). Participants will be free to withdraw consent at any time without prejudice to current or future medical care. When a participant expresses his/her wishes to withdraw from the study, he/she will receive instructions to complete an “end of study” visit, which will also be voluntary. Data collected up to the time of withdrawal will remain in the trial database and be included in data analysis.

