### Relevant concomitant care permitted or prohibited during the trial {11d}

Hypoglycemic drugs, insulin, and medications known to affect body weight will not be allowed during the trial. If a participant must use any of these medications, he/she will be withdrawn from the study. The principal investigator will determine acceptability of any other concomitant medication. Adolescents in this study will continue to receive conventional lifestyle management advice as per routine clinical practice at their clinics.

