## Assignment of interventions: blinding

### Who will be blinded {17a}

Both participants and research team will be blinded to the type of intervention allocated to each arm until the end of the study. The group not on MET (fiber alone) will receive a placebo pill (MCC). The group not on fiber will also receive a placebo (MCC) in identical sachets; this double-blind strategy will reduce risk of bias. Both fiber and MET have a similar side-effect profile, which will support the blinding procedures.

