#### Methods in analysis to handle protocol non-adherence and any statistical methods to handle missing data {20c}

We will undertake an intention-to-treat analysis to assess intervention effect.

Multiple imputation approach or a sensitivity analysis will be followed to address missing data.

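### Intolerance, early antibiotics, HbA1c above 8% or prohibited drugs end study participation, not only study product, so the intention-to-treat analysis loses HOMA-IR values that could have been measured

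*Protocol article*

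**What the plan says.** The section on discontinuing or modifying allocated interventions {11b} has one action for every criterion: "Participants will be withdrawn from the study if the participant (1) withdraws consent, (2) becomes pregnant", and so on through the list. That list includes a participant who "does not tolerate either MET or dietary fiber interventions, (4) requires antibiotic therapy within the first 6 months of the trial", one who "has an HbA1c > 8"%, and one who, in the investigator's opinion, cannot continue, for example because insulin is needed.

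Two other sections repeat the action. On metformin titration: "those who do not tolerate will be withdrawn from the study". On hypoglycemic drugs, insulin and weight-affecting medication, in the concomitant care section {11d}: "If a participant must use any of these medications, he/she will be withdrawn from the study".

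On what is kept: "Data collected up to the time of withdrawal will remain in the trial database and be included in data analysis". A closing visit is described in {11b} and in the retention section {18b}, but only for participants who themselves wish to leave; {11b} adds that it is voluntary.

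The section on non-adherence and missing data {20c} states: "We will undertake an intention-to-treat analysis to assess intervention effect". It then offers multiple imputation or a sensitivity analysis for missing data. The Outcomes section {12} places HOMA-IR at baseline, 6 and 12 months.

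**The concern.** No section lets a participant stop study product and stay in follow-up. Metformin reaches full dose after 4 weeks and fiber after 3, so intolerance is likely to appear early. Anyone withdrawn then has no scheduled HOMA-IR after baseline. An analysis plan cannot repair this, because it cannot use values the protocol stops collecting.

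Two of the reasons may be related to arm or outcome. The combination arm takes both active products, so its participants have two possible sources of intolerance. HbA1c above 8%, or a need for insulin or hypoglycemic drugs, follows glycemic response, which the trial expects to differ between arms. Antibiotic use is different: there the main problem is the avoidable loss of a primary outcome value.

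At stake are some bias in the comparison of arms and an attrition allowance spent partly on participants who were still available for measurement.

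**Working it through.** **Inputs from the protocol article.** Design effects of 0.75 and 0.86 SD, 26 per arm taken as feasible, 15% attrition and 90 in total (Sample size {14}); 30 per arm (Trial design {8}). The article gives no withdrawal rates by reason or by arm, so all rates below are assumptions.

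**Step 1: the plan's own figure.** 26 × 1.15 = 29.9, so 30 per arm and 90 in total, as stated. (Dividing instead, 26 / 0.85 = 30.6, gives 31 per arm.) With 15% loss, 30 × 0.85 = 25.5 per arm remain. The 15% is a single allowance for attrition during follow-up, with nothing added for withdrawals that the protocol itself requires.

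**Step 2: what loss costs in power.** Two-sided 5% t-test, two arms, 30 randomised per arm:

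| Loss | n per arm | Power at 0.75 SD | Power at 0.86 SD |
|---|---|---|---|
| 0% | 30 | 81.5% | 90.6% |
| 15% | 25.5 | 74.7% | 85.3% |
| 25% | 22.5 | 69.1% | 80.5% |

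Each further 5 points of loss costs roughly 2 to 3 points of power. The first row assumes that off-product values leave the effect size unchanged.

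**Step 3: assumed loss by arm.** If intolerance to the two agents is independent, loss in the combination arm is 1 − (1 − a)(1 − b).
- 10% for each agent: 1 − 0.90 × 0.90 = 19%, against 10% in each monotherapy arm.
- 5% for each agent: 1 − 0.95 × 0.95 = 9.75%, against 5%.

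**Step 4: bias of a completer comparison.** If leavers are k SD worse than those who stay, an arm's completer mean is too favourable by (proportion lost) × k. The bias in the contrast is then (difference in loss) × k.
- 10% against 19%: 0.09 × 0.5 = 0.045 SD and 0.09 × 1 = 0.09 SD. Divided by 0.75, this is 6% and 12%.
- 5% against 9.75%: 0.0475 × 0.5 = 0.024 SD and 0.0475 × 1 = 0.048 SD, or 3% and 6%.
- Equal loss with an equal gap: 0.

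**Step 5: upper case.** Suppose exactly the highest HOMA-IR values are lost in both arms. For a normal outcome, removing the top fraction q lowers the mean by φ(z)/(1 − q) SD, where z is the upper-q point.
- q = 10%: 0.1755 / 0.90 = 0.195.
- q = 19%: 0.2714 / 0.81 = 0.335.
- Net: 0.335 − 0.195 = 0.14 SD, or 19% of 0.75.

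**The case against.** **Arm-dependence is not established.** The article gives no rates. Its Background {6a} cites a study in adults in which adding a product with inulin, oat β-glucan and blueberry polyphenolics to metformin improved gastrointestinal tolerance after 2 weeks. That was a different mixture and population, but it points away from worse tolerance of the combination. The fiber section expects good tolerance with dose escalation. The blinding section adds "Both fiber and MET have a similar side-effect profile", which bears on balance between the two monotherapy arms but not on the combination arm. This objection stands: both the size and the direction of any imbalance are unknown.

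**Glycemic withdrawals lose less than it seems.** As described, the 3-month visit has no blood draw, and HbA1c comes from the same fasting samples as glucose and insulin. An HbA1c above 8% found at a study visit would thus come with a HOMA-IR from that visit: at month 6 only the 12-month value is lost, and at month 12 nothing. The mixed model or imputation can then condition on the poor observed value. This largely stands, with two limits: the schedule table is not shown, and clinical testing between visits could trigger withdrawal. It does not help participants withdrawn for intolerance before month 6.

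**Intention-to-treat is not abandoned.** A reader might infer that the withdrawal rules contradict the promised analysis. They do not: data before withdrawal are included and missing data are addressed. It is a missing-data weakness built into follow-up, and imputation remains a poorer substitute for a value that could have been measured.

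**Later antibiotics are not wholly unregulated.** A reader might infer that no rule exists after month 6. Section {11d} leaves other concomitant medication to the principal investigator. What is absent is a stated treatment of antibiotic exposure in the 12-month stool endpoints.

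**Conclusion.** The point holds as an avoidable loss of primary outcome data, written into three sections and not reconciled with {20c}. The avoidable loss is certain for anyone withdrawn under these rules who would still have consented to measurement. The bias is only possible: about 0.045 to 0.09 SD (6-12% of the 0.75 design effect) under an assumed 10% against 19% loss with leavers 0.5 to 1 SD worse, and about 0.14 SD if the highest values are lost in both arms. It is nil if loss and gap are equal across arms, and its direction is not certain.

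A reader might reach a larger figure by removing the top 10% or 15% of one arm and nobody from the others, which shifts that arm by 0.20 or 0.27 SD, or 26-37% of the design effect. The documents do not support this. Nothing in them links gastrointestinal intolerance to HOMA-IR, and loss in one arm only is not a realistic reading of the criteria.

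The change should be made; the article reports that recruitment had not started.

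**What to change.** Leave the clinical criteria for stopping product untouched, and reconcile the metformin titration section, {11b} and {11d} with {20c} as follows.

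- Separate stopping study product from leaving the study. Where a criterion is met but consent remains and it is clinically acceptable, continue the scheduled 6- and 12-month HOMA-IR assessments.
- Include HOMA-IR measured off product in the intention-to-treat analysis.
- Pre-specify separate handling of values obtained after insulin or hypoglycemic drugs are started. HOMA-IR is built from fasting glucose and fasting insulin, so such values are hard to interpret and should not simply be pooled.
- Keep antibiotic users in the HOMA-IR analysis. Address antibiotic exposure only within the stool-derived endpoints, by the same rule at 6 and 12 months.

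The cost is protocol wording, a few extra visits that are already on the schedule, and possibly slight dilution of the effect by off-treatment data.
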